## Methods and analysis

### Trial design

This protocol describes the methodology of a parallel-group, two-arm randomized controlled trial, which will employ an intervention condition (CALMA app) and a control condition (Treatment as usual-TAU) with a 3-month follow-up for each participant. Participants will be assessed at four timepoints: day-0 (baseline), day-30, day-60, and day-90.

The intervention group will receive the CALMA app and continue with the usual treatment in a public hospital mental health service. The CALMA app will be downloaded with the assistance of a team member into the participant’s smartphone during the first interview. In each follow-up interview (30-days and 60-days), the use of the app will be reinforced. The control group (TAU) will not receive the app but will keep doing the usual treatment provided in public hospitals throughout the study. The usual treatment in public hospitals in Argentina consists of a weekly visit to a psychologist and a monthly visit to a psychiatrist (in case the patient receives any pharmacological treatment). In the public hospitals of Argentina, there are no DBT programs, and most of the interventions are psychoanalytic.

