### Intervention

#### Implementation of the intervention

CALMA is an app for smartphones that interacts with the user, providing evidence-based tools to prevent suicide; it is openly available and free to download on Apple or Google market place. It was developed, with contribution of mental health professionals, by our research group which are also mental health professionals. CALMA is based on the DBT program, which is one of the third-wave cognitive-behavioral therapies and seeks to train consultants with self-injurious behavior with and without suicidal intent in emotional regulation skills in order to manage their emotions more effectively (13, 55). CALMA integrates DBT strategies in two modalities: “Out of crisis” in which the user has some vulnerability reduction strategies to reduce the probability of crisis appearance, and the “I Need Help” modality (aimed at helping the user in crisis) constituted first with problem-solving strategies (DBT always gives the opportunity to solve the problem that triggered the crisis) and then, if the intensity of the crisis does not decrease, it implements distress tolerance or emotional regulation DBT skills dependent on the level of distress rated by the user (concept derived from the *breaking point* of DBT skills). A detailed description of the development of CALMA has been described elsewhere (51). All the features of CALMA app are based on face-to-face interventions that have shown efficacy in the reduction of self-injurious behavior and that are part of the central axis of the DBT program such as problem-solving (54), emotion regulation (13, 55, 56), distress tolerance (13, 55, 56) and also access to emergency contacts at the time of the crisis (31, 35). The app offers these interventions sequentially, and users can select which to employ. To guarantee the fidelity of the CALMA app to the model, DBT therapists have been included as stakeholders in the design of the intervention. Also, participants’ opinion was considered (52). In the management of an emotional crisis, the CALMA app follows the steps of crisis management and telephone coaching, initially going through the problem-solving strategy until reaching discomfort tolerance or emotional regulation skills as self-management strategies (11, 57, 58). The “Out of Crisis” modality consists of four functions that are identified in the initial screen of the app (Figure 1). The “Moments” function is based on the Inventory of Reasons to Live (59), considering that reasons for living reduce the risk of suicide (59, 60). In “Moments,” the user can add photos, videos, audios, songs, phrases, or anything that generates well-being and works as an anchor to life. The (b) “Agenda” function is based on evidence that positive events, such as pleasurable activities, serves as a protective factor for SI, thus reducing vulnerability to future suicidal crises (61). Moreover, engagement in positive events serves as a buffer between stressful adverse events and SI (62). The (c) “Profile” function provides the option for the user to add names and telephone numbers of people who can be contacted during a crisis if the crisis is not able to be resolved with the “Emergency Card” (see later). The (d) “Tips” function provides psychoeducational material related to suicidal crises and how to prevent unwanted behaviors during these crises. The user receives a weekly notification as a reminder of these sections. The “I need help” modality consists of interventions based on DBT skills. The skills were designed to be easily accessed during a crisis by the user activating the “I need help” button at the bottom of the home screen. All interventions are presented in a card format.

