##### Engagement with the app

Engagement will be determined by three parameters: acceptability, subjective use, and objective use. For acceptability, the User Experience Questionnaire will be used in its short version (UEQ-s) (75). The UEQ-s scale contains 8 items that evaluate the app’s pragmatic qualities (attractiveness, clarity and reliability) and hedonic qualities (novel, stimulating). Each item is scored on a Likert scale from 0 to 7, with antagonistic qualities being found at their extremes (0 and 7). Subjective use will be assessed with 5 directed questions are asked with the possibility of a dichotomous response (Yes/No); (“Did you use the app when you were in crisis?”; “In case you used it, was it useful for crisis management?”; “Did you use the app outside of times of crisis? crisis?”; “Do you consider that this modality “out of crisis” helped you to prevent the appearance of new crises?”; “Would you recommend the application to other people?”).

Objective use of the app will be obtained and recorded *via* the participant’s phone number. Specifically, use will be recorded when at least one of the following features of CALMA is used during the study period: opened a “Tips,” arrived at the “Emergency Card,” finished a crisis (due to success or abandonment), opened a notification, added a contact, reviewed their “Moments,” added a picture or content to their “Moments,” closed the app while it was in crisis and ended a crisis successfully. In addition, patients will be defined as “users” of the app if they met the following criteria: subjectively reported using the app in the survey and used at least one feature recorded by our objective measures. Finally, the relationship between the content of the app used by the participants and the primary outcome will be evaluated.

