### Participant timeline

Clinicians will be asked to draw up a list of patients who have presented self-injurious behavior in the last month. With this list, the patients will be identified on the days that they attend the control by their psychiatrist or psychologist of each Service. After the usual control of the patient, one of the members of the research group will explain the purpose of the study to the participant and legal guardian. Next, the researcher will give them a copy of the consent and/or assent to read carefully and invite them to participate in the study. After the invitation, those who agree to participate will be scheduled for a 30-min interview with one of the research group members.

The first interview will be face-to-face and it will determine if the participant meets the inclusion criteria and sign the informed consent. Then, a series of clinical and demographic data will be requested and the Spanish version of the Self-Injurious Thoughts and Behaviors Interview (SITBI) and the Difficulties in Emotion Regulation Scale (DERS) will be administered. At the end of the interview, the follow up interviews will be scheduled and those patients randomized to the intervention group will have the application downloaded to their cell phones. In addition, they will be given a brief 5 to 10-min tutorial on how the app works, they will be given written material on its functioning, and they will be directed to the website where there will be explanatory material.^1^

Follow-up interviews (day-30 and day-60): those will be conducted *via* video call according to the epidemiological context of the COVID-19 pandemic. During these calls, only the SITBI will be administered and participants will be asked if they have had any hospitalization due to suicidal behavior in that period, and if so, the date of admission. In the intervention group, to guarantee engagement with the CALMA app, the rater will explore whether or not the participant has used the application. In case of not using it, the obstacles and the alternatives to overcome them will be determined through a brief protocol (DBT missing links strategy) to reinforce the use of the application during the next evaluation period. At the same time, the technical team will work throughout the study to guarantee the proper functioning of the app.

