The final interview (day-90) will be face-to-face or by video call depending on the epidemiological context of the COVID-19 pandemic. The SITBI, the DERS and, to those who received the app, the User Experience Questionnaire short version (UEQ-s) and a series of questions related to the opinion about the app will be administered. At the end of this interview, we will obtain data from the patient about the frequency of use of the app (subjective use report) and our information technology team will also obtain data on the use of the different functionalities of the app from each participant (objective use report). A flowchart describing how an individual participant will progress through the phases of the research process is outlined in Figure 6.

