### Safety procedure

A strict suicide safety protocol will be followed given our participant eligibility criteria. Patient safety will be the highest priority in this study. Included in the CALMA app’s “Emergency Card” is a linked directory of major crisis helplines and a geolocation feature of emergency services near the user’s location, allowing participants to connect directly to these services.

A suicide safety assessment will be carried out in each interview, where the SITBI will be administered. Under the circumstance that the patient is at risk, the interviewer (a psychiatric member of the research group) will alert the parent and indicate that he/she accompany the participant to the Emergency Department of the center where the recruitment was carried out to be evaluated by a mental health professional. The interviewer also will alert the study coordinator ([name]) and will alert the research collaborator at each recruitment center. Each collaborator will immediately notify to the emergency room physician on call that day for an acute psychiatric assessment so that said clinician can contact the participant’s parent, guaranteeing the presence of the patient in the emergency department. In addition, each collaborator will notify the patient’s pediatric medical team of each hospital.

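### UEQ-s ratings and the usefulness and recommendation answers may be biased upward, because the group that built the app and reinforced its use also collects them

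*Protocol article*

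**What the plan says.** Acceptability is named in the General objective. Describing engagement is one of the secondary specific objectives. Under Engagement with the app, engagement has three parts: acceptability (the eight-item UEQ-s), subjective use and objective use. On the second part the article says: "Subjective use will be assessed with 5 directed questions are asked", each answered yes or no. Two of the five ask about use (in crisis, outside crisis), two about usefulness, and one about recommending the app.

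The people involved are described in several places:

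- **Developer.** Implementation of the intervention says of the app: "It was developed, with contribution of mental health professionals, by our research group which are also mental health professionals".
- **Interviewer.** Safety procedure describes what happens at each interview where the SITBI is given: "the interviewer (a psychiatric member of the research group) will alert the parent". Participant timeline lists the SITBI at day 90.
- **Reinforcement.** Trial design says: "In each follow-up interview (30-days and 60-days), the use of the app will be reinforced". Participant timeline adds: "to guarantee engagement with the CALMA app, the rater will explore whether or not the participant has used the application". With a participant who has not used the app, obstacles and ways round them are then worked through.
- **Collection of opinions.** At the day-90 interview the UEQ-s is given, "and a series of questions related to the opinion about the app will be administered", and self-reported use is obtained from the patient.

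The information technology team separately extracts feature-level use from the app. A participant counts as a user only with both a self-report of use and at least one logged feature. Under Statistical analysis, the UEQ results are placed in one of five benchmark categories in order to judge CALMA against other products.

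**The concern.** Patients aged 10 to 19 are asked for their opinion of an app at an interview run by a psychiatrist from the group that made it. Two earlier interviews have treated non-use as a problem to be solved. In that setting some respondents can be expected to answer more favourably than they would in private.

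Only app recipients are asked, so no comparison arm could cancel such a shift. An upward bias in the UEQ-s would pass directly into the benchmark category. An upward bias in the usefulness and recommendation items would pass into the reported percentages. A favourable acceptability result would then be open to the criticism that it partly reflects politeness.

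**Working it through.** The plan states no figure on this point, so there is none to reproduce. The check has three steps.

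**1. Is the link from developer to day-90 interviewer stated?** Yes, by joining three sections. Implementation of the intervention makes the research group the developer. Safety procedure makes the interviewer at each SITBI interview a member of that group. Participant timeline places the SITBI, the UEQ-s and the opinion questions in the same day-90 interview. The line in Participant timeline that patients are "scheduled for a 30-min interview with one of the research group members" concerns the first interview only, so the day-90 link rests on Safety procedure.

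**2. Which items have an independent check?**

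| Item | Control arm | Logged counterpart |
|---|---|---|
| UEQ-s (8 items) | none | none |
| Usefulness (2 questions) | none | none |
| Would recommend (1 question) | none | none |
| Used in crisis | none | yes: crisis episodes finished or abandoned, Emergency Card reached |
| Used outside crisis | none | yes: Tips, Moments, contacts, notifications |

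The exposed set is the UEQ-s and three of the five questions. For the two use questions, over-reporting alone cannot make a user of someone with no logged activity. The log is nevertheless a low bar. Opening one notification counts as a feature, and the app sends a weekly reminder: 90 / 7 = 12.9, so about 12 occasions during follow-up. Among participants who tapped one reminder, self-report alone decides user status.

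**3. How large could it be?** The documents cannot answer this.

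- *Granularity.* Sample size plans 29 per group with 15% loss: 29 × 0.85 = 24.65, about 25 respondents. One changed answer moves a percentage by 1/25 = 4 points. It moves more for the question on usefulness in crisis, which applies only to those who used the app then.
- *Illustration under an assumption.* Let p be the true proportion who would privately recommend the app, and c the share of private refusals that become a yes in front of the interviewer. Then reported = p + c(1 − p). Both values are assumed. With p = 0.60, c = 0.10 gives 0.60 + 0.10 × 0.40 = 0.64, and c = 0.30 gives 0.60 + 0.30 × 0.40 = 0.72.
- *UEQ-s.* No corresponding shift in score or benchmark category can be calculated, because the documents give neither the category limits nor an expected score.

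**The case against.** The strongest reply is that the article does not say how the UEQ-s is completed. It uses the same verb, administered, for the DERS, a 36-item scale with first-person items, and it calls the source of self-reported use a survey. Self-completion may already be intended and set out in the full protocol. This stands for the UEQ-s. It has less force for the five questions, which the article says are asked. Even a form filled in during the interview is not private unless that is arranged.

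Three further replies stand:

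- Logged use is collected and enters the definition of a user, so self-reported use is partly checked.
- Acceptability is a descriptive outcome in one arm, with no test or success threshold stated.
- Answers coded by study ID still return to the developer group. Self-completion removes the interviewer's presence but does not make the assessment independent.

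A reader might infer two stronger claims that the documents do not support. One is that the ratings will be inflated; nothing in the article shows that this happens or how much. The other is that the same individual reinforces use and then collects the ratings; the article places both tasks within the trial team but does not say one person does both.

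**Conclusion.** The point holds as a plausible risk of upward bias in the UEQ-s ratings and in the usefulness and recommendation answers. It rests on the stated roles of the research group as developer and day-90 interviewer, on the reinforcement at days 30 and 60, and on the absence of any described private collection.

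Its size is unknown. The 64% to 72% illustration depends wholly on the assumed 10% to 30% conversion rate and the assumed true value of 60%, and it does not carry over to the UEQ-s benchmark category. It would be wrong to treat self-reported use as equally exposed, given the logs and the two-source definition of a user. The primary comparison of self-injurious behaviours and the sample size are not affected by this point. It is a worthwhile, inexpensive improvement and not a flaw that threatens the trial.

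**What to change.** In Engagement with the app and in the day-90 paragraph of Participant timeline, state that app-arm participants complete the UEQ-s and the five questions themselves, on their own phone, at the day-90 assessment. Answers should be coded by study ID and not be visible to the interviewer. The form should prompt for blank items before it is submitted. The instruments, their wording and the assessment day stay as planned, and the form works equally for a face-to-face or a video interview. In reporting, show self-reported use beside logged use, so that a reader can see where the two disagree.

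Eligibility already requires a smartphone, so the cost is a short web form and a sentence or two of procedure, with no extra visit. The downside is a few more blank items than with an interviewer. Among about 25 respondents that is not negligible, because a missing self-report also leaves user status undetermined; the prompt is there to limit this.

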**Figure 6 fig6:**
[figure not shown]
Flow of participants.

### Sample size

The sample size was calculated using the G*Power 3.1.9.4 statistical software according to the main objective. Considering a confidence level of 95%, a power of 80% and an effect size *d* = 0.85, 25 individuals per group are needed to detect a significant difference in the median frequency of self-injurious behaviors with the two tailed Mann–Whitney U test. Assuming a proportion of lost in the follow-up of 15%, then the study would have to start with 29 individuals per group.

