### Specific objectives

#### Primary specific objectives

Compare the change in the frequency of self-injurious behaviors in the participants who receive the app with the frequency in those who do not receive the application.

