### Outcomes measures

#### Primary outcome measure

Suicidal behavior will be assessed using the Spanish version of the Self-Injurious Thoughts and Behaviors Interview (SITBI) (68, 69). This is a structured interview consisting of 169 items divided into 5 modules that examine the presence, frequency and characteristics of 5 types of self-injurious behavior: (a) suicidal ideation; (b) suicide plans; (c) suicidal gestures; (d) suicide attempts and (e) self-harm. The SITBI conceptualizes suicide risk on a continuum, starting with suicidal ideation (“thoughts of killing yourself?”), possibly accompanied by a suicide plan [“think about how you might kill yourself (e.g., taking pills, shooting yourself) or work out a plan of how to kill yourself?”] and in some cases by suicide attempt [“made a suicide attempt (i.e., purposefully hurt yourself with at least some intent to die)?”]. The construction of the questions in the original SITBI is consistent with the commonly accepted definitions of each type of behavior. The administration of the scale takes between 3 and 15 min.

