### Statistical analysis

To describe the sociodemographic characteristics of the patients in the two groups, absolute and relative frequencies (%) will be used for the qualitative variables, and the mean and standard deviation will be used for the only quantitative variable (age) if it presents a normal distribution according to the Shapiro–Wilk test. In case of presenting a non-normal distribution, the median and the interquartile range will be computed.

To compare the sociodemographic characteristics between the groups, the chi-square or Fisher’s exact test will be used for the qualitative variables, and the student’s t-test or the Mann–Whitney U test will be computed for the quantitative variable.

For all patients and at each follow-up moments, the difference between the frequency of each suicidal behavior and the baseline frequency will be calculated. Then it will be evaluated if these differences follow a normal distribution (Shapiro–Wilk test). In this case, the mean differences for each behavior between both groups will be compared using the t-Student test. Otherwise, the medians will be compared with the Mann–Whitney U test. The *p*-values obtained will be corrected according to the Bonferroni criterion.

To assess whether the change in emotional regulation mediates the change in the frequencies of each suicidal behavior, the difference between the value of the DERS scale at the last follow-up and the baseline will be calculated, and the Sobel test will be used on a regression model whose dependent variable will be the difference in the frequency of each behavior and the independent variable will be the treatment. Previously, the probability distribution of the quantitative variables will be evaluated and it will be considered whether it is necessary to carry out any transformation of data to guarantee compliance with the assumptions of the regression model.

Both for the frequencies of the different suicidal behaviors and for the DERS scale, the missing values will be imputed according with the multiple imputation method using chained equations (MICE) with appropriate models for each variable to be imputed, considering sociodemographic characteristics, the hospital of recruitment and the baseline measurements of frequencies and DERS scale as independent variables.

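### The 80% power is for one test at two-sided 0.05, but the analysis Bonferroni-corrects a set of tests by behaviour and visit whose size is not stated; power for any one comparison is about 67%, 52% or 45% for 3, 9 or 15 tests

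*Protocol article*

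**What the plan says.** **Sample size.** The calculation is for the main objective and is introduced by "Considering a confidence level of 95%, a power of 80" per cent, with d = 0.85. It concludes that "25 individuals per group are needed to detect a significant difference in the median frequency of self-injurious behaviors", "with the two tailed Mann–Whitney U test". Allowing for 15% loss, 29 per group are enrolled. Multiplicity is not mentioned.

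**Statistical analysis.** For all patients, "at each follow-up moments, the difference between the frequency of each suicidal behavior and the baseline frequency will be calculated". The groups are then compared on each behaviour by a t-test or, if the differences are not normal, a Mann–Whitney test. The p-values "obtained will be corrected according to the Bonferroni criterion". Significance is declared below 0.05. The number of tests in the correction is not stated.

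**What counts as primary.** The primary specific objective is to "Compare the change in the frequency of self-injurious behaviors in the participants who receive the app" with that in participants who do not. Self-injurious thoughts come under the secondary objectives. The Primary outcome measure section, however, describes the SITBI modules, which "examine the presence, frequency and characteristics of 5 types of self-injurious behavior", and two of those five are suicidal ideation and suicide plans. The Trial design section gives three post-baseline assessments: days 30, 60 and 90.

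**The concern.** The sample size assumes that the primary question is answered by one test at 0.05. The analysis splits that question by behaviour and by visit and divides the significance level among the tests. A Bonferroni-corrected test at 0.05/m is harder to pass than the one that was powered, so the same 25 per group cannot give 80% for it at the same d.

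Two things are at stake. First, the stated power would not describe any comparison actually made. In a small trial in high-risk adolescents, a non-significant result could then be read as evidence that the app does not work when the test had a substantial chance of missing the assumed effect. Second, with no behaviour and no visit designated, a reader cannot tell beforehand which result answers the primary objective.

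**Working it through.** **Inputs.** From Sample size: d = 0.85, two-sided 0.05, 25 evaluable and 29 enrolled per group, Mann–Whitney test. From Trial design: 3 follow-up visits. From Primary outcome measure: 5 SITBI types; from the eligibility definition under Subjects: 3 behaviours (attempt, gesture, self-injury). Two inputs are my assumptions: the number of tests m, which the protocol does not give, and a normal parent distribution, which it does not state.

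**Formula** (asymptotic relative efficiency method, as in G\*Power). With A = 3/π = 0.955 for a normal parent and n per group:
- degrees of freedom = 2nA − 2
- noncentrality = d × √(nA/2)
- power = probability that a noncentral t variable exceeds the two-sided critical value at 0.05/m in absolute value

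**Step 1: reproduce the plan's figure (m = 1).** At n = 24 power is 80.3%. At n = 25, nA = 23.87, df = 45.7, noncentrality = 0.85 × √(23.87/2) = 2.94, critical t = 2.01, and power = 82.0%. The stated 25 is therefore within one participant of the result at an undivided 0.05. Other parents give 23 (plain t-test), 27 (minimum efficiency), 21 (logistic) and 16 (Laplace). On loss, 25 × 1.15 = 28.75 and 25/0.85 = 29.4, so 29 is reproduced to within one.

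**Step 2: possible families.**
- m = 3: the correction runs over visits only, or over three behaviours only
- m = 9: 3 behaviours × 3 visits
- m = 15: 5 SITBI types × 3 visits, which needs thoughts to share the correction

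**Step 3: power for one comparison at 0.05/m** (d = 0.85, normal parent).

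| m | Level | Critical t (n = 25) | Power, n = 25 | Power, n = 29 | Evaluable n per group for 80% | Enrolled n per group (÷ 0.85) |
|---|---|---|---|---|---|---|
| 1 | 0.0500 | 2.01 | 82.0% | 87.4% | 24 | 29 |
| 3 | 0.0167 | 2.48 | 67.4% | 75.3% | 32 | 38 |
| 9 | 0.0056 | 2.91 | 51.6% | 60.9% | 40 | 48 |
| 15 | 0.0033 | 3.10 | 44.6% | 54.0% | 44 | 52 |

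The n = 29 column is an upper bound. The plan imputes missing frequencies, but imputation does not fully restore the information lost.

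**Step 4: check by simulation.** 20,000 simulated Mann–Whitney tests on normal data at 25 per group gave 81.4% (m = 1), 66.6% (m = 3), 50.7% (m = 9) and 43.0% (m = 15).

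**Step 5: sensitivity to the parent.** For m = 3 to m = 15 at 25 per group, power falls from 62% to 39% (minimum efficiency), 70% to 47% (t-test) and 75% to 53% (logistic). A heavy-tailed Laplace parent gives 89% to 74%, but under it the plan would have needed 16 per group, so it does not fit the stated 25.

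**The case against.** **The family is not defined, and its definition may be left to an analysis plan.** This is right as far as it goes. The text does not say whether Bonferroni runs over behaviours, visits or both, so no single power figure can be pinned on the trial. But the protocol itself fixes both the correction and the power. Over 3 or more tests, the two do not fit together under the assumptions that reproduce 25. An analysis plan could resolve this only by narrowing the primary test or restating the power.

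**The 15-test family is the weaker reading.** This stands. The five types describe the instrument, and the objectives place thoughts among the secondary aims. The 45% figure applies only if thoughts share the correction; the text allows this but does not say it.

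**A reader might infer that the trial would miss the assumed effect about half the time.** That holds only for one comparison named in advance, under a family of 9 to 15. If every comparison truly had d = 0.85, the simulated chance of at least one corrected significant result at 25 per group is about 77% to nearly 100%, with correlations between comparisons of 0.8 down to 0. This does not rescue the stated power, because the protocol does not define success as any one significant result and the Sample size section describes one comparison.

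**More than 25 per group may be analysed.** With imputation, up to 29 could contribute. This narrows the gap but, with a normal parent, does not close it for any of the three families.

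**Conclusion.** The point holds as an inconsistency between multiplicity and power. It is not an arithmetic error: 25 per group is reproduced to within one for a single test at 0.05. Under the planned Bonferroni correction, power for any one comparison at 25 per group is about 67%, 52% or 45% for 3, 9 or 15 tests, with upper bounds of 75%, 61% and 54% at 29 per group. These figures rest on d = 0.85 for the comparison in question, a normal parent and an assumed family size.

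A reader might also infer that d = 0.85 is unattainable for rare behaviours such as attempts, because most changes would be zero. The documents do not support that: they give no rate for attempts, and the answer depends heavily on the rate assumed. It forms no part of this conclusion.

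**What to change.** Make one of two changes before unblinded data are examined.

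1. **Name one primary test (preferred).** Specify one measure of self-injurious behaviour and one time point or window, expressed as change from baseline in line with the primary objective. One example is the combined frequency of attempts, gestures and non-suicidal self-injury at day 90. Test it at 0.05, and make the behaviour-specific, other-visit and thought comparisons secondary. The existing calculation then matches the analysis. A combined count weights different acts equally and may be driven by the commonest one, so the choice of measure should be justified.

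2. **Keep the Bonferroni family.** State which behaviours and visits it covers, and restate the power in the Sample size section at the corrected level: about 67%, 52% or 45% for 3, 9 or 15 tests at 25 per group.

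Either change needs wording only, with no extra participants or data. The cost of the first is that the other comparisons lose primary status; the cost of the second is a less favourable stated power.
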